### Procedures

#### Study 1

A national deployment will be conducted in collaboration with all partners and youth centers. Recruitment will be facilitated via email distribution. Young residents of Youth transition Centers across the country will receive an email from the National Union for Youth Housing (Union Nationale pour l’Habitat des Jeunes: UNHAJ). This email will include detailed information about the research and a link to access the study. Upon accessing the study’s homepage, participants will encounter an introductory note outlining the study, its objectives, a contact point for further information, and a link to open the questionnaire. Clicking the link will direct them to a consent form with a binary choice: “Yes” or “No,” responding to the question: “Do you consent to participate in this research?“. Participants who select “Yes” will activate the questionnaire and proceed with the study, while those who select “No” will not be able to participate.

#### Study 2

The qualitative study will focus on a sample of young residents from all the structures involved in this research. Inclusion criteria require participants to be adults, French-speaking, and affected by substance use issues. Participants who consent to take part in the study, after reviewing the information notice provided at least 15 days prior to the first interview to allow for reflection, will meet with one of the investigators from the research team. The investigator will present the consent form, detailing the study’s objectives, methodology, duration, potential constraints, and foreseeable risks, while addressing any questions from the participant.

Each participant will undergo three sessions of approximately one hour each: a semi-structured interview, administration of the Rorschach test, and the Adult Attachment Interview (AAI). All interviews will be conducted by the same investigator who conducted the initial session to foster a trusting environment. The study in each structure will be conducted in a secure and confidential setting for participants. All three sessions will be audio-recorded using a voice recorder, transcribed, anonymized, and subsequently destroyed to ensure confidentiality.

#### Study 3

The longitudinal study will follow the same inclusion criteria as the qualitative study (Study 2). However, participation in the group sessions is open to all volunteers for each session, regardless of whether they are substance users. Informed consent will be systematically obtained before each session, ensuring fully informed participation. Promotion of the groups will be conducted through widespread dissemination of informational posters, email communications via the management of the partner structures, and during informational meetings. A follow-up meeting will be organized 15 days later to conduct the initial T0 evaluation with the volunteers.

The “Well-Being coffee group” intervention is implemented in several formats (see Fig. 1). Some groups will take place in person, others via videoconference, all conducted by the same psychologist throughout the sessions. Additionally, a control group will consist of participants who underwent the initial evaluation (T0) but did not attend any sessions. The inclusion of this control group allows for the assessment of changes in psychological and behavioral outcomes over time, comparing those who received the intervention to those who did not. The choice of this comparator was made based on feasibility and ethical considerations, ensuring that participants were not deprived of potential care while maintaining an adequate framework for evaluating the intervention’s effects. Across all formats, participation is voluntary, following a prior information phase and the signing of an informed consent form. Participants will complete standardized evaluation questionnaires at multiple time points (T0, T1, T2, T3).

The discussion groups aim to provide a supportive and open space for free expression. Their objective is to allow participants to articulate their thoughts, emotions, and personal experiences, as well as those evoked by group discussions on various themes, including identity, substance use, migratory experiences, and mental health. The impact of the intervention will be assessed regularly using standardized tools to measure levels of anxiety, depression, and changes in attitudes and willingness to seek help. Finally, a global satisfaction scale will be used at the end of the sessions to collect participants’ subjective feedback on their experiences within the groups (see Fig. 1).

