Participants are assessed at multiple time points (T0: prior to the program, T1: mid-program, T2: end of the program, T3: post-program follow-up). These longitudinal evaluations, based on standardized tools, will enable a detailed analysis of participants’ well-being progression and the specific effects attributable to the group intervention. This study is part of an action-research framework, integrating clinical intervention with the production of scientific knowledge while offering transferable recommendations for other support programs aimed at vulnerable young adults.

**Table 1 Tab1:** Summary table of the research methodology

	Study 1	Study 2	Study 3
Type of study	Quantitative	Qualitative	Longitudinale
Method	Cohort study using self-administered questionnaires	Semi-structured interviews Rorschach test Adult Attachment interview (AAI)	Group intervention Self-administrated questionnaires
Eligibility criteria	Participant aged > 18 Resident in a Housing center Fluent in French adult participants who are not under guardianship (tutelle) or curatorship (curatelle).	Participant aged > 18 Fluent in French Any substance user Migratory background	Same as study 1
Exclusion criteria	Minors Do not speak and read French Under Guardianship or Curatorship	Minors Do not speak and read French Under Guardianship or Curatorship	Minors Do not speak and read French Under Guardianship or Curatorship
Main Outcomes	Substance use prevalence Mental health representations Mental health aspects (anxiety, depression) Childhood trauma	Substance use, trauma and migration trajectory (semi-structure interview) Attachment style (AAI tool) Psychological functioning (Rorschach test)	Substance use Perception of mental health care Wellness
Analysis	Quantitative analysis	Thematic analysis	Quantitative and qualitative analysis

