A semi-structured interview guide was developed based on a review of existing literature and preliminary interviews. The questions focus on participants’ life narratives and their experiences with substance use. The administration of the Rorschach test and the Adult Attachment Interview (AAI) will also be conducted. The Rorschach test is a “projective” psychological assessment composed of 10 cards depicting black-and-white and color inkblots. It allows for the assessment of an individual’s psychological functioning concerning certain fundamental competencies expressed through their engagement with the test material, such as their perception style, emotional expression, approach to interpersonal relationships, and significant individual characteristics and issues that reflect a singular mode of psychological organization [48]. The Adult Attachment Interview (AAI) is a 20-question interview designed to assess an individual’s attachment representations based on their recollections of early caregiving experiences. The responses are transcribed and analyzed using a rigorous coding system, classifying individuals into attachment categories such as secure, dismissing, preoccupied, or unresolved regarding trauma or loss [49, 50].

#### Study 3

**Generalized Anxiety Disorder (GAD-7)** [51–53]: A 7-item self-report questionnaire designed to assess the patient’s anxiety levels over the previous two weeks.

**Patient Health Questionnaire-9 (PHQ-9)** [54, 55]: A 9-item tool used for depression screening that also provides an indication of the severity of depressive symptoms.

**Alcohol Use Disorders Identification Test (AUDIT)** [41, 42]: A 10-item questionnaire designed to determine whether an individual is at risk of alcohol addiction. The items assess alcohol consumption, dependency, and related problems.

**Fagerström Test for Nicotine Dependence** [43, 44]: A 6-item questionnaire created to evaluate the level of nicotine dependence among smokers.

**Cannabis Abuse Screening Test (CAST)** [45]: A screening tool designed to identify problematic cannabis use, particularly among adolescents and young adults. It consists of six questions addressing consumption habits and associated problems over the past 12 months.

**Attitudes Toward Seeking Professional Psychological Help Short Form (ATSPPH-S)** [56, 57]: A 10- items psychometric scale designed to measure individuals’ attitudes toward seeking professional psychological help.

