### Data analysis

#### Study 1

The research team will conduct statistical analyses using R. The cross-sectional study will characterize the study population through descriptive and multivariate analyses (e.g., Chi-square/Fisher’s exact tests, correlation tests, ANOVA, etc.). We will adhere to the STROBE guidelines for epidemiological studies [58]. A significance level of 0.05 will be applied for statistical analysis.

#### Study 2

A thematic analysis of the data from the semi-structured interviews will be conducted using NVivo 15 software. Moreover, the findings from the Rorschach test will be analyzed using a methodology for interpreting projective material [48], with the aim of highlighting underlying psychic processes, particularly those related to attachment dynamics early traumas, the defensive mechanisms of participants. Additionally, the interviews reported from the AAI assessment will be coded by MN and AF under the supervision of a certified reliable coder [name] using the Adult Attachment Scoring and Classification System [49].

#### Study 3

For the group intervention, a Bonferroni correction will be applied to all *p*-values in t-tests. Cronbach’s alpha will be used to assess the reliability of the scales. Various analyses will be conducted to evaluate pre- and post-intervention effects as well as dose-response effects, including Student’s t-tests, repeated-measures ANOVA, and linear regression.

Primary and secondary outcomes will be analyzed using linear mixed models, incorporating a random group effect if estimation permits. The primary outcome measure is the variation in the total score on the ATSPPH-S at 9 months, calculated using dimensional scoring algorithms. Changes in the primary outcome and the relative effectiveness of the four intervention modalities will be assessed using mixed regression models, utilizing all available data while accounting for participant, time, and group levels. The underlying distribution for the mixed regression model will be determined based on residual distribution.

Per-protocol analyses will also be performed to test robustness. ANCOVA analyses may be conducted as needed to control for confounding variables that could influence the results. If data distribution is non-parametric, analyses such as Mann-Whitney, Wilcoxon, and Kruskal-Wallis tests will be employed.

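### Study 3 compares self-selected arms on substance-use scales in a mix of users and non-users without committing to account for T0 use, so unequal user shares can bias the between-arm change

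*Protocol article*

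**What the plan says.** **Outcome.** Table 1 (Methods/design) gives the main outcomes of Study 3 as "Substance use Perception of mental health care Wellness". Objective 4 in the Background concerns preventing the risks of substance use. Data analysis, Study 3, names the ATSPPH-S at 9 months as the primary outcome, so substance use is a main but not a primary outcome.

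**Who takes part.** Procedures, Study 3, first applies the Study 2 inclusion criteria, which require substance use. It then says that "participation in the group sessions is open to all volunteers for each session, regardless of whether they are substance users". Table 1 instead sets Study 3 eligibility equal to that of Study 1, which does not require use.

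**Arms.** They are not randomised: "a control group will consist of participants who underwent the initial evaluation (T0) but did not attend any sessions".

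**Scales (Measures, Study 3).**
- AUDIT: "The items assess alcohol consumption, dependency, and related problems".
- CAST: "It consists of six questions addressing consumption habits and associated problems over the past 12 months".
- Fagerström: "A 6-item questionnaire created to evaluate the level of nicotine dependence among smokers".

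**Analysis.** "Primary and secondary outcomes will be analyzed using linear mixed models". No user subset, no stratification by use and no T0-use covariate is named. ANCOVA for confounders is optional and lists no covariates.

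**The concern.** Someone who does not use a substance at T0 sits at or near the floor of its scale. That person can stay there or get worse, but has almost no room to improve. A user can move in either direction. The mean change in an arm therefore depends on how many users it holds as well as on what the sessions do. Even a sample of users would be mixed on each scale, because a user of one substance need not use the others.

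People decide for themselves whether to attend, and the sessions discuss substance use among other themes, so unequal user shares between arms are plausible. A participant-level random effect absorbs differences in starting level. It does not absorb a difference in average change that comes from composition.

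Two further problems follow:
- Reduction among users and onset among non-users bear on different claims, and in one mean they can offset each other.
- The Fagerström test is described for smokers, and the article does not say what score a participant receives after stopping. If that value is treated as missing, the most favourable result leaves the analysis.

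At stake is a reported effect, or lack of effect, of the groups on substance use that reflects who was in each arm.

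**Working it through.** **Inputs from the protocol article.** 55 per modality, 165 in total and 182 with dropout (Participants, Study 3); non-randomised arms; three use-dependent scales; linear mixed models.

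**Assumed inputs.** The share of users in each arm and the change over time among users. The documents give neither, so ranges are shown.

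**Step 1: the plan's own figure.** With d = 0.7 and two-sided alpha 0.05, the exact two-sample t-test needs 54.02 per group at 95% power, hence 55. The article states neither the power nor the sidedness. 3 × 55 = 165, and 165 × 1.10 = 181.5, hence 182. The calculation names no scale and is not tied to substance use. It is used here only for subset sizes.

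**Step 2: mean change in one arm.** Let p be the share of users at T0, c_U the mean change in users and c_N the mean change in non-users:

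mean change = p × c_U + (1 − p) × c_N

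Only if c_N = 0 does this reduce to p × c_U. A 1-point fall in users then shows as 0.2, 0.3 or 0.5 points at p = 0.2, 0.3 or 0.5.

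**Step 3: between-arm contrast with no intervention effect.** Let users change by the same c in both arms and non-users not change:

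attenders minus controls = (p_A − p_C) × c

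| p_A (attenders) | p_C (controls) | c | Spurious difference |
|---|---|---|---|
| 0.3 | 0.6 | −2 | 0.3 × (−2) − 0.6 × (−2) = +0.6 (favours control) |
| 0.6 | 0.3 | −2 | 0.6 × (−2) − 0.3 × (−2) = −0.6 (favours the groups) |
| 0.4 | 0.5 | −2 | 0.4 × (−2) − 0.5 × (−2) = +0.2 (favours control) |
| any | equal to p_A | any | 0 |
| any | any | 0 | 0 |

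The bias needs both unequal shares and some change among users. Its direction depends on which arm holds more users.

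**Step 4: the same scenario conditional on T0 use.** Among T0 users the contrast is −2 − (−2) = 0. Among T0 non-users it is 0 − 0 = 0. Any weighted average of the two is 0, so stratifying by T0 use removes this bias.

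**Step 5: blending.** At p = 0.3, a 2-point fall in users contributes 0.3 × (−2) = −0.6. A mean rise of 0.6 / 0.7 = 0.86 points in non-users cancels it exactly. The arm then shows no change, although users improved and some non-users started.

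**Step 6: size of the user stratum.** At an assumed 30% users, 0.30 × 55 = 16.5, about 17 per modality.

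**The case against.** **The handling of T0 use may sit in a full protocol or SAP that is not shown.** This has weight for scoring rules and subset definitions, and the absence of such detail is not the point. The article itself combines a use-dependent main outcome, open attendance, self-selected arms and a stated model. That combination can give a wrong between-arm result.

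**The primary outcome is untouched.** This stands. A reader might infer that the main result of Study 3 is compromised. The documents do not support that: the primary outcome is the ATSPPH-S, which does not depend on use, and the sample size is not tied to the substance scales.

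**The plan has tools that could help.** ANCOVA on T0 values would lessen the bias, but it is optional and no covariate is named. Choosing the model distribution from the residuals, or falling back on rank tests, addresses the shape of floor-heavy scores and leaves composition as it is.

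**The all-participant mean is a legitimate quantity.** This stands for the prevention objective, where onset counts. The estimate should be kept, adjusted for T0 use. It cannot by itself support a claim of reduction.

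**Non-users might attend without belonging to the research sample.** The sentence applying the Study 2 criteria allows that reading, while Table 1 contradicts it. Even then, each scale would include people who do not use that particular substance.

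**Selecting T0 users invites regression to the mean.** True for pre/post tests within one arm. It operates in both arms of the between-arm contrast, so it does not defeat that comparison.

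**Power.** One might infer that admitting non-users wrecks power. Take a 0.7 SD effect in users and 55 per arm. Power falls from 95% with all users to 45% at 30% users if non-users add no variance, or to 19% if the SD is unchanged. But analysing only the 17 or so users per arm gives about 51%, so under zero non-user variance dilution costs little against the realistic alternative. Bias and interpretation are the issue.

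**Conclusion.** The point holds for the substance-use outcomes of Study 3 and should be corrected before analysis. The between-arm difference in mean change is biased by (p_A − p_C) × c when user shares differ and users change over time. Under the assumed 30% versus 60% and a common 2-point fall, that is 0.6 points in favour of control; with 40% versus 50% it is 0.2. These shares and the fall are illustrations, and the documents do not show that the arms will differ by that much.

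Two stronger readings go too far. The overall estimate is not in general the effect in users times their share, because that requires no change in non-users, who may start using. Nor do the documents show that participants who stop smoking will be lost; they leave the Fagerström score after stopping undefined, which makes the loss possible.

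**What to change.** 1. For AUDIT, CAST and Fagerström separately, define T0 use of that substance and analyse the between-arm change stratified by it and adjusted for the T0 score.
2. Base any claim of reduction on the between-arm contrast in the T0-user stratum, not on pre/post change within one arm.
3. Report onset among T0 non-users as a proportion per arm, for the prevention objective.
4. Still report the all-participant estimate, adjusted for T0 use.
5. For Fagerström only, score T0 smokers who report having stopped as 0 rather than missing. Keep observed AUDIT and CAST scores. CAST looks back 12 months, so someone who stopped recently can have a valid non-zero score.
6. Reconcile the two Study 3 eligibility statements (Table 1, same as Study 1; Procedures, same as Study 2 but sessions open to all) so that the analysis population is clear.

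**Cost.** This is analysis wording on scales already collected at T0. Item 5 also needs current smoking status at each assessment, if the questionnaire does not already record it. The strata are small (about 17 of 55 per modality at an assumed 30% users), so intervals will be wider. Stratifying by T0 use does not remove other confounding from self-selection into the arms.

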## Methods/design

This research project is therefore structured around three complementary phases of study (Table 1), each based on a distinct methodological approach:

A **cross-sectional study (study 1)** that relies on a quantitative approach, conducted through the dissemination of online standardized questionnaires and scales (see: Measures) to young adults residing in partner structures at both regional and national levels. Its objective is to identify factors associated with addictive behaviors and to explore the links between trauma, migratory trajectories, food insecurity, psychological distress and perceived representations and barriers to accessing psychological care. These tools enable the rigorous collection of quantitative data and a multidimensional assessment to model the relationships between factors associated with the psychological and social challenges faced by this population. This study provides insights into general statistical trends.A **qualitative study (study 2)** adopting an exploratory perspective and aiming an in-depth understanding of the representations, subjective experiences, and individual and relational dynamics associated with addictive behaviors and trauma. The qualitative study builds upon the findings of Phase 1 by collecting clinical insights that provide a deeper understanding of the subjective dynamics of participants dealing with substance use issues and the obstacles encountered in their life trajectories that shape their relationship with care services.A **longitudinal study (study 3)** structured around a group intervention called the “Well-Being coffee group”, which operates as an open group (8 to 12 participants per session), conducted over six sessions, each lasting 1.5 to 2 h, held in the evening (6–8 PM) once a month for six months. Participation is voluntary for young residents in THP. The study aims to evaluate the impact of this group discussion format on participants’ psychological well-being, their perceptions of mental health, and their access to care.

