Furthermore, the central aspect of this research lies in integrating the cultural dimension into understanding issues related to substance use and implementing group-based interventions. Numerous studies have underscored the importance of cultural adaptation in general and specifically in the treatment of substance use disorders [69–71]. However, this approach remains limited if it is not accompanied by efforts to raise young people’s awareness of the importance of mental health care.

We therefore expect an improvement in the well-being of young participants engaged in group-based interventions and a positive shift in their perceptions of psychological care, potentially leading to an increased demand for such services. Additionally, virtual group settings are expected to enhance accessibility and strengthen the effectiveness of interventions.

Ultimately, this research project aspires to develop comprehensive, evidence-based intervention and prevention strategies, aimed at more effectively addressing the specific needs of young residents in transitional youth centers.

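### Study 3 compares the effectiveness of group formats, yet the shown text gives no chance allocation of format and lets volunteers join session by session; unless Fig. 1 or the full protocol randomises format, the comparison is observational.

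*Protocol article*

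**What the plan says.** Procedures, Study 3, describes two kinds of delivery: "Some groups will take place in person, others via videoconference, all conducted by the same psychologist throughout the sessions". On entry it says that "participation in the group sessions is open to all volunteers for each session, regardless of whether they are substance users", and that "Across all formats, participation is voluntary, following a prior information phase and the signing of an informed consent form". Methods/design describes an open group of 8 to 12 people per session, with six monthly sessions.

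Data analysis, Study 3, names the change in ATSPPH-S total score at 9 months as the primary outcome and says that "the relative effectiveness of the four intervention modalities will be assessed using mixed regression models". The Discussion adds that "virtual group settings are expected to enhance accessibility and strengthen the effectiveness of interventions".

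The control is defined by non-attendance: "a control group will consist of participants who underwent the initial evaluation (T0) but did not attend any sessions". A reason is given for that choice: "The choice of this comparator was made based on feasibility and ethical considerations, ensuring that participants were not deprived of potential care". No reason or rule is given for how format is assigned.

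On confounding, Data analysis offers ANCOVA as an option and names no covariates. The mixed models account for participant, time and group, with a random effect for group where it can be estimated.

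**The concern.** A claim that one format works better than another needs the people in the two formats to be comparable, or the differences between them to be measured and adjusted for. The visible text secures neither. Entry is voluntary and renewed at each session, and no step links a participant to one format.

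The outcome makes this more serious. ATSPPH-S measures attitude toward seeking psychological help, and the Background describes reluctance and stigma around such help among these residents. Willingness to sit in a room with others, or to join online instead, may well be related to that attitude. The Discussion itself expects the virtual format to improve access, which means reaching people who would otherwise not come. If format changes who attends, a better score online may reflect the attenders and not the format.

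Modality is also central to the plan: the sample size is set per modality, and the primary mixed model compares modalities.

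**Working it through.** **1. What the text says about allocation.** The abstract, Methods/design, Table 1, Procedures and Data analysis were compared. None mentions a random draw of persons, groups or residences to a format. Procedures points to Fig. 1 for the formats, and that figure is not shown. The finding is therefore conditional on Fig. 1 and the full protocol.

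**2. The plan's own figure.** Participants, Study 3, gives d = 0.7, significance level 0.05, 55 per modality, 165 in total and 182 recruited. Power and sidedness are not stated. A two-sided two-sample t-test with n = 55 has noncentrality 0.7 × √(55/2) = 0.7 × 5.244 = 3.67 on 108 degrees of freedom, which gives power 0.953. At power 0.95 the required n is 55, so the figure is reproduced. 3 × 55 = 165, and 165 × 1.10 = 181.5, which rounds up to 182. (Dividing instead, 165/0.9 = 183.3, gives 184.) Nothing in this calculation protects against selection. The 165 covers three modalities while the analysis section speaks of four; that mismatch is a separate matter.

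**3. What selection could do (illustration).** Assume no true format effect, 55 per format, no clustering, and a difference of b SD between the people in the two formats that remains in the outcome contrast after any adjustment. The noncentrality is b × √(55/2) = 5.244b.

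| b (SD, assumed) | noncentrality | chance of a significant two-sided 5% test |
|---|---|---|
| 0.1 | 0.52 | 8% |
| 0.2 | 1.05 | 18% |
| 0.3 | 1.57 | 34% |
| 0.5 | 2.62 | 74% |

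Relative to the planned effect, 0.2/0.7 = 29% and 0.3/0.7 = 43%. The article does not say which contrast the 0.7 refers to, so this ratio gives scale only.

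**4. What mixing could do (illustration).** If 20% of each format's sessions were attended in the other format, and effect were proportional to exposure, the contrast retained would be 1 − 0.2 − 0.2 = 0.6 of the true difference.

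**5. What a draw of whole groups would involve.** With stable groups of 8 to 12, 55 people make 55/12 = 4.6 to 55/8 = 6.9, so about 5 to 7 groups per format. With an assumed intraclass correlation of 0.01 to 0.10, the design effect runs from 1 + 7 × 0.01 = 1.07 to 1 + 11 × 0.10 = 2.10. That gives 55 × 1.07 = 58.9, so 59, to 55 × 2.10 = 115.5, so 116 per format.

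**The case against.** The strongest reply is that silence is not a statement. Fig. 1 is the Study 3 flowchart, where an allocation step would normally appear, and a journal article leaves detail to the full protocol. This stands, and it is why the point is conditional. It does not remove the point, because randomisation of format would be a leading design feature and no visible section mentions it, while the entry rule that is stated does not by itself fix a format per person.

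Four stronger readings are tempting, and the documents do not support them.

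- *Format is confounded with residence.* No section says that format is set by residence or that support differs between formats. A videoconference group could draw on several residences.
- *Participants switch between formats.* Open entry describes who may join. It permits switching but does not say that it happens.
- *The plan gives an inadequate reason for not randomising format.* It gives a reason for choosing non-attenders as comparator and none about format. That reason would not stand in the way of drawing format by lot, since every format delivers the group, but the authors do not use it that way.
- *The expectation about virtual groups is an error.* A directional expectation in a Discussion is legitimate. It matters only because the design may not be able to test it.

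The plan also has partial safeguards. One psychologist conducts all groups, which removes differences between facilitators. A random group effect addresses clustering, and ANCOVA could adjust for measured confounders. None of these removes unmeasured selection, and the ANCOVA is optional with no covariates named.

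**Conclusion.** The point holds in conditional form. On the visible text, the format comparison on the primary outcome is observational and open to selection, and a relative-effectiveness conclusion would go further than the design allows. If Fig. 1 or the full protocol randomises format and ties each person to one format, the point falls.

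The size of any bias cannot be derived from the documents. The 0.1 to 0.5 SD imbalances, the 20% mixing and the intraclass correlations are assumptions chosen to show scale and carry no evidential weight. They show that a modest residual difference between attenders, 0.2 to 0.3 SD, would be enough to raise the false-positive rate from 5% to about 18% to 34%.

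The point is limited to one format against another. The comparison with non-attenders raises its own questions and is not judged here.

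**What to change.** First, state how format is assigned. If a random rule exists in the full protocol, cite it. Otherwise:

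1. Define each participant's modality once, as the format offered at T0, and analyse by it whatever is later attended. State at the same time how people who were offered a format but attended no session are handled, since the article places them in the control.
2. Make adjustment for baseline ATSPPH-S and the other T0 scores (GAD-7, PHQ-9, AUDIT, Fagerström, CAST) mandatory in the mixed model. Enter residence as a random effect where it can be estimated. Fixed residence effects should not be used if each residence hosts one format, because they would be collinear with format.
3. Report the format contrast as observational and exploratory, not as relative effectiveness, except for any groups whose format was drawn at random.
4. Optionally, draw the format at random for groups not yet started, where a site can host either format.

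Steps 1 to 3 use data already collected and cost little beyond a documented change to the analysis. Their downside is a weaker format claim, and analysis by the format offered keeps whatever dilution arises when people attend the other format. Step 4 costs more: it needs a protocol amendment and reduces freedom in scheduling the one psychologist. It can cover only part of the study, since recruitment began in January 2025 and was due to end in December 2025. With about 5 to 7 groups per format it would balance only roughly, and clustering would still have to be allowed for.
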